## Methods and analysis

### Aims

Develop an adaptive, scalable, self-administered, digital comprehensive cognitive screening tool to detect cognitive impairments in patients with cerebrovascular disease. The IC3 will:Detect both domain-general (eg, executive function) and domain-specific (eg aphasia, apraxia, neglect) deficits poststroke.^10^Allow monitoring to occur at scale, in a cost-efficient manner, as test administration can occur independent of trained professionals.Minimise the effects of neglect or aphasia on cognitive assessments.Have high test–retest reliability for repeated-testing longitudinally.Validate the IC3 against commonly used cognitive screening tools.Use IC3 in a cohort of stroke survivors to map the cognitive recovery trajectory over the course of the first year after stroke.Identify novel biomarkers of cognitive outcome (at 1 year) and recovery trajectory through the main study using:Demographics, and comorbid physical, neuropsychological and socioeconomic factors.Structural and functional MRI brain imaging, to assess metrics of cerebrovascular disease load, stroke lesion topology and brain network dynamics.Blood biomarkers of Alzheimer’s disease (phosphorylated tau forms and amyloid β42/40 ratio), neuroaxonal injury (neurofilament light, NFL and brain-derived tau) and astrocytic activation (glial fibrillary acidic protein, GFAP). The study will characterise the time course of these biomarkers over the first year after stroke and relate these to MRI measures of axonal injury and brain atrophy, as well as cognitive and functional outcomes.

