#### Main IC3 study design

This prospective observational longitudinal study aims to recruit 300 patients with acute stroke and obtain repeated measures of cognition and psychosocial status at baseline, 3 months, 6 months and 12 months postictus. IC3 is currently a single-site study at Imperial College Healthcare NHS Trust, England, and commenced recruitment in February 2022. In addition to the cognitive monitoring, all patients will be invited to take part in MRI brain imaging and blood biomarker substudies (figure 3; see substudies for more details).

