### Outcome measures

The primary outcome measure for cognition will be the IC3-derived accuracy measures for each primary cognitive domain listed in table 1 at 1-year post ictus. Secondary outcome measures will be (a) MOCA score,^15^ (b) functional measures including National Institute of Health Stroke Scale,^23^ Modified Rankin Scale,^24^ Instrumental Activities of Daily Living^14^ and (c) psychological measures via the Geriatric Depression Scale^13^ and Apathy Evaluation Scale.^7^

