### Data analysis plan

#### Cognition

Dimensionality reduction techniques, such as principal component analysis, graph-based methods and hierarchical clustering will examine the inter-relationship between cognitive domains and will be used to derive latent variables. These will be used to relate to blood and imaging biomarkers. Such cognitive profiling will also form the basis for future real-time optimisation of the IC3 task presentation based on patients’ performance.

To assess the trajectories of functional, clinical and psychological outcome measures, we will employ linear mixed effect models. These models will include cognitive measures as the main predictors, together with standard covariates such as age, sex, lesion and initial cognitive deficit.

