#### Blood biomarkers

NFL, GFAP, amyloid and tau biomarkers will be analysed to describe their dynamics after acute stroke and to compare differences between groups. Additionally, longitudinal changes in these biomarkers will be assessed within patients using non-parametric tests, where appropriate. The relationship between blood biomarker levels and continuous outcome measures at 1 year (eg, cognitive scores) will be investigated using mixed-effects linear regression. For binarised outcome measures (eg, favourable or unfavourable MRS scores), logistic regression will be employed.

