### Brain imaging

The following analyses will be performed to derive imaging predictors of cognition and relate to blood biomarker levels: (1) WMHV evaluated using FSL Brain Intensity Abnormality Classification Algorithm package (https://fsl.fmrib.ox.ac.uk/fsl/fslwiki/BIANCA); (2) stroke lesion topology manually delineated on FLAIR images; (3) NODDI measures of axonal injury and tissue microstructure (fractional anisotropy, neural density and orientation dispersion index) analysed in NODDI MATLAB Toolbox; (4) Cortical thickness measured using Freesurfer; (5) vascular reactivity analysis^18^ and (6) Resting-state fMRI analyses of the effect of stroke on functional brain networks. These measures will be compared between groups. Longitudinally, each patient will act as their own ‘control’ in linear regressions accounting for age, sex, initial stroke severity, lesion volume and time. Finally, structural equation modelling will be used to determine the relationship between demographics, comorbidities, blood and brain imaging biomarkers and cognitive and functional outcome measures.

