#### Sample size

The primary blood biomarker predictor is NFL. Based on preliminary reported group differences,^19^ we expect 140 patients at baseline, and 60 patients at 3-months poststroke (when peak NFL is expected to occur), will be able to detect group differences in NFL levels between patients and controls (Wilcoxon Mann Whitney test, Cohen’s d=0.38 and 0.58, respectively, alpha=0.05, power=0.8, one tailed, allocation ratio 2:1). A much smaller sample size of 56 will be enough to detect correlations between NFL and time of sampling of the acute blood: (r^2^=0.10,^19^ alpha=0.05, power=0.8, one tailed).

The primary imaging outcome measure is WMHV. A sample size of 80 will be sufficiently powered to detect correlation between NFL and WMHV based on preliminary findings^25^ (r=0.32, alpha 0.05, power 0.95). A sample size of N=70 will be sufficiently powered to detect the relationship between peak plasma NFL levels and binary functional outcomes (based on similar effects observed after acute brain injury (R^2^=0.28,^26^ α=0.05, power=0.9). Expecting a 20%–25% lost to follow-up rate (due to patient factors and technical factors), the stated sample size of 200 in blood biomarker substudy is sufficiently powered to detect all the above-mentioned effects.

A secondary blood biomarker predictor is raised phosphorylated tau. Based on the mean and SD reported for longitudinal change in phosphorylated tau (N=374) in population of elderly cognitively normal population,^27^ a sample size of N=65, will have 95% power in detecting any true change in mean over 1-year period (α=0.05, effect size 0.41). Thus, the stated sample size is sufficiently powered to detect longitudinal change in phosphorylated tau.

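### No stated model of 1-year cognition adjusts for baseline cognition, so a marker of the acute deficit cannot be told apart from a marker of recovery

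*Protocol article*

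**What the plan says.** All places are in the protocol article.

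- **Aims:** one aim is to "Identify novel biomarkers of cognitive outcome (at 1 year) and recovery trajectory through the main study". It names two targets, the level reached at 1 year and the course of recovery.
- **Outcome measures:** the primary cognitive outcome is the "IC3-derived accuracy measures for each primary cognitive domain listed in table 1 at 1-year post ictus".
- **Main IC3 study design:** the study will "obtain repeated measures of cognition and psychosocial status at baseline, 3 months, 6 months and 12 months postictus". A baseline value on the outcome instrument is therefore planned.
- **Data analysis plan, Blood biomarkers:** "The relationship between blood biomarker levels and continuous outcome measures at 1 year (eg, cognitive scores) will be investigated using mixed-effects linear regression". No covariate of any kind is named.
- **Brain imaging:** the section opens with the purpose of deriving imaging predictors of cognition. Its longitudinal analyses use each patient as their own control in "linear regressions accounting for age, sex, initial stroke severity, lesion volume and time". The response variable is not stated. A structural equation model then links demographics, comorbidities, blood and imaging markers to cognitive and functional outcomes. Baseline cognition is not named in it.
- **Data analysis plan, Cognition:** "To assess the trajectories of functional, clinical and psychological outcome measures, we will employ linear mixed effect models". Cognitive measures are the main predictors there, together with "standard covariates such as age, sex, lesion and initial cognitive deficit".

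**The concern.** The only models for which initial cognitive deficit is named as a covariate are those in which cognition is the predictor. Where the 1-year cognitive score is the response, no stated model includes its own baseline value.

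This matters because early and late cognition are correlated. A blood or imaging marker that merely reflects how impaired the patient was in the first days will be associated with the 1-year score through that correlation alone. It could then be reported as a biomarker of recovery, or as a useful predictor, while adding nothing to the IC3 test planned at the same visit. The abstract says the study should identify the patients with the greatest potential for recovery. That question concerns change given the starting point, and an unadjusted model does not answer it.

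**Working it through.** The article gives no power or sample size for a marker against 1-year cognition, so there is no stated figure to reproduce. The check asks how often a marker with no information beyond baseline would appear significant.

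**Inputs from the article (Sample size section)**

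- "the stated sample size of 200 in blood biomarker substudy", with expected loss of 20%–25%: 200 × 0.80 = 160 and 200 × 0.75 = 150.
- Alpha 0.05, taken here as two-sided.

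**Assumptions, since the article gives neither value**

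- r_mb, the correlation of marker with baseline score: 0.2 to 0.3.
- rho, the correlation of baseline with 1-year score: 0.5 to 0.7.

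**Step 1: unadjusted association.** If the marker is linked to the 1-year score only through baseline, the marginal correlation is r = r_mb × rho. Examples: 0.2 × 0.5 = 0.10; 0.3 × 0.7 = 0.21.

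**Step 2: probability of significance, by Fisher z.** P = Φ(√(N−3)·atanh(r) − 1.96) + Φ(−√(N−3)·atanh(r) − 1.96).

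For N = 150 and r = 0.15: √147 × atanh(0.15) = 12.124 × 0.1511 = 1.83, and Φ(1.83 − 1.96) = 0.45. The second term is negligible.

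| r_mb | rho | Marginal r | P, N = 150 | P, N = 160 |
|---|---|---|---|---|
| 0.2 | 0.5 | 0.10 | 0.229 | 0.242 |
| 0.2 | 0.7 | 0.14 | 0.401 | 0.423 |
| 0.3 | 0.5 | 0.15 | 0.449 | 0.474 |
| 0.3 | 0.7 | 0.21 | 0.734 | 0.761 |

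**Step 3: adjusted association.** The partial correlation given baseline is (r − r_mb·rho) / √((1 − r_mb²)(1 − rho²)). With r = r_mb·rho the numerator is zero, so the adjusted test rejects at its nominal 5%. This takes the marker to be related to the baseline score as measured. Measurement error in baseline IC3 would leave some of the induced association in place.

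**Step 4: precision.** Adjustment multiplies the residual variance by about 1 − rho². The standard error of the marker coefficient changes by about √((1 − rho²)/(1 − r_mb²)). With r_mb = 0.3:

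| rho | Residual variance factor | Standard error ratio |
|---|---|---|
| 0.3 | 0.91 | 1.00 |
| 0.5 | 0.75 | 0.91 |
| 0.7 | 0.51 | 0.75 |

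At rho = 0.3 nothing is gained. The gain depends on a correlation that the article does not give.

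**The case against.** Several points on the other side stand, and they limit what can be said.

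- **Silence in the Blood biomarkers section.** A reader might infer that the plan deliberately leaves baseline IC3 out. The text does not support that. The sentence names no covariates at all, not even age, and a condensed article may leave them to the full protocol or analysis plan. The Cognition section's list is open-ended and calls initial cognitive deficit standard, so adjustment may be intended.
- **Imaging response not stated.** The regressions may model the imaging measures themselves, in which case baseline IC3 is not the baseline of the outcome. Stroke severity and lesion volume are also partial proxies for the initial deficit. Neither, however, is the same-domain score. The own-control design does not fill the gap for the study's research MRI measures, since those scans are at 3 and 12 months only.
- **Mixed effects.** A joint model of all visits would carry the starting level, but the stated response is the outcome at 1 year and no earlier score is mentioned.
- **The unadjusted association is real.** A reader might take 23%–76% as a false-positive rate. For the 1-year-level aim it is power to detect a true total association, and early cognition may lie on the path from injury to outcome. The figures are an error rate only if the result is read as evidence on recovery or added value.
- **Baseline availability.** A reader might assume that every patient has a baseline IC3. It is planned for all, but the article says the tool has limited applicability in severe deficits, and patients with severe aphasia may enter through a consultee.
- **Structural equation model.** It is described by broad classes of variable, so not naming baseline cognition there is weak evidence by itself.

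**Conclusion.** The point holds in a limited form. No model in the article is stated to adjust 1-year cognition for baseline cognition, although another part of the same analysis plan calls that covariate standard and its measurement is planned. Followed as written, the models answer the 1-year-level aim but cannot separate a marker of the acute deficit from a marker of recovery or of added prognostic value.

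Under the assumed correlations, a marker with nothing to add beyond baseline reaches significance about 23%–76% of the time unadjusted, against about 5% adjusted. That is roughly 5 to 15 times nominal when read as a recovery claim (0.23/0.05 = 4.6; 0.76/0.05 = 15.2). The size rests wholly on those assumptions. It would be wrong to conclude that precision is necessarily lost, since the gain from adjustment can be nil. The change is worth making because it is nearly free and bears directly on a stated aim.

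**What to change.** 1. In the Blood biomarkers and Brain imaging sections, wherever a 1-year IC3 domain score is the response, add a model with the patient's baseline IC3 score for the same domain as a covariate.
2. State the response variable of the longitudinal imaging regressions, so that it is clear where this applies, and align the covariates across the Cognition, Blood biomarkers and Brain imaging sections.
3. Include baseline cognition in the structural equation model.
4. Base claims about recovery or added prognostic value on the adjusted model, reporting the marker's incremental R² over the baseline score.
5. Keep the model without baseline for the total association with the 1-year outcome, and label it so.
6. State how patients without a usable baseline IC3, for example those with severe deficits, are handled; multiple imputation is one option.

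The change is to analysis wording and needs no assessment beyond those planned. It costs one degree of freedom per model and the handling of missing baselines. Reported associations will probably be smaller for markers that mainly reflect initial severity.

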### Brain imaging

The following analyses will be performed to derive imaging predictors of cognition and relate to blood biomarker levels: (1) WMHV evaluated using FSL Brain Intensity Abnormality Classification Algorithm package (https://fsl.fmrib.ox.ac.uk/fsl/fslwiki/BIANCA); (2) stroke lesion topology manually delineated on FLAIR images; (3) NODDI measures of axonal injury and tissue microstructure (fractional anisotropy, neural density and orientation dispersion index) analysed in NODDI MATLAB Toolbox; (4) Cortical thickness measured using Freesurfer; (5) vascular reactivity analysis^18^ and (6) Resting-state fMRI analyses of the effect of stroke on functional brain networks. These measures will be compared between groups. Longitudinally, each patient will act as their own ‘control’ in linear regressions accounting for age, sex, initial stroke severity, lesion volume and time. Finally, structural equation modelling will be used to determine the relationship between demographics, comorbidities, blood and brain imaging biomarkers and cognitive and functional outcome measures.

#### Sample size

The primary blood biomarker predictor is NFL. Based on preliminary reported group differences,^19^ we expect 140 patients at baseline, and 60 patients at 3-months poststroke (when peak NFL is expected to occur), will be able to detect group differences in NFL levels between patients and controls (Wilcoxon Mann Whitney test, Cohen’s d=0.38 and 0.58, respectively, alpha=0.05, power=0.8, one tailed, allocation ratio 2:1). A much smaller sample size of 56 will be enough to detect correlations between NFL and time of sampling of the acute blood: (r^2^=0.10,^19^ alpha=0.05, power=0.8, one tailed).

The primary imaging outcome measure is WMHV. A sample size of 80 will be sufficiently powered to detect correlation between NFL and WMHV based on preliminary findings^25^ (r=0.32, alpha 0.05, power 0.95). A sample size of N=70 will be sufficiently powered to detect the relationship between peak plasma NFL levels and binary functional outcomes (based on similar effects observed after acute brain injury (R^2^=0.28,^26^ α=0.05, power=0.9). Expecting a 20%–25% lost to follow-up rate (due to patient factors and technical factors), the stated sample size of 200 in blood biomarker substudy is sufficiently powered to detect all the above-mentioned effects.

A secondary blood biomarker predictor is raised phosphorylated tau. Based on the mean and SD reported for longitudinal change in phosphorylated tau (N=374) in population of elderly cognitively normal population,^27^ a sample size of N=65, will have 95% power in detecting any true change in mean over 1-year period (α=0.05, effect size 0.41). Thus, the stated sample size is sufficiently powered to detect longitudinal change in phosphorylated tau.

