#### MRI substudy

Clinically acquired brain imaging at the time of the acute stroke (including fluid-attenuated inversion recovery (FLAIR) and diffusion-weighted imaging sequences) will be obtained. All 300 patients will be invited to undergo additional brain MRI imaging at 3 and 12 months using a Siemens Verio 3T scanner at the Imperial College Clinical Imaging Facility. MRI measures will be used as prognostic indicators for cognitive trajectory. MRI data will be collected from additional 50 age-matched control participants for comparison. The following sequences will be acquired at each session over 60–90 min (breaks included):

Structural MRI: T1 (1 mm^3^ resolution for volumetric analyses of lesion volume and brain atrophy); susceptibility weighted imaging (0.8×0.8×3.0 mm^3^ for identification of microbleeds); T2 FLAIR (1 mm^3^ for detecting white matter hyperintensity volume (WMHV)); and neurite orientation dispersion and density imaging (NODDI, an advanced multishell diffusion MRI with 90 directions and 9 b_0_ images) to assess axonal integrity and tissue microstructure. Lesions will be defined using established standards.^17^Functional MRI: Resting-state and breath-hold paradigm will measure dynamic regional brain activity and vascular reactivity, respectively.^18^

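### The power of 0.95 stated for the NFL–WMHV correlation does not follow from N=80 and r=0.32: those inputs give about 0.83–0.85 two-sided or 0.90–0.91 one-sided

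*Protocol article*

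**What the plan says.** The Sample size section of the protocol article states: "The primary imaging outcome measure is WMHV". It then gives one power calculation for that measure: "A sample size of 80 will be sufficiently powered to detect correlation between NFL and WMHV based on preliminary findings", with the inputs "r=0.32, alpha 0.05, power 0.95". The number of tails is not given for this line. The two calculations just before it, the NFL group comparison and the correlation of NFL with sampling time, both carry "alpha=0.05, power=0.8, one tailed".

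The paragraph ends by drawing the calculations together. It starts from "Expecting a 20%–25% lost to follow-up rate" and concludes that "the stated sample size of 200 in blood biomarker substudy is sufficiently powered to detect all the above-mentioned effects".

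The MRI substudy section says: "All 300 patients will be invited to undergo additional brain MRI imaging at 3 and 12 months". The article gives no expected MRI uptake.

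**The concern.** N, r, alpha and power are all stated in the same line, and any three of them fix the fourth once the number of tails is chosen. The line can therefore be checked without any other document, and no separate analysis plan could make inconsistent figures agree. Read against the other calculations in the section, 80 looks too few for 0.95 power at a correlation of this size.

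At stake is the only power statement for the primary imaging measure. A reader would take the risk of missing a true correlation of 0.32 with 80 patients to be 5%, when it is about 15–17% two-sided or 9–10% one-sided. The line is also one of the effects that the closing statement about 200 blood patients claims to cover.

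**Working it through.** **Inputs** (protocol article, Sample size): N=80, r=0.32, alpha=0.05, stated power 0.95. The tails are not stated, so both cases are worked.

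**1. Power at N=80 by Fisher z.** Power = Φ(atanh(r)·√(N−3) − z_α).
- atanh(0.32) = 0.3316; √77 = 8.775; product = 2.910.
- Two-sided: Φ(2.910 − 1.960) = Φ(0.950) = 0.829.
- One-sided: Φ(2.910 − 1.645) = Φ(1.265) = 0.897.

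The plan's 0.95 is not reproduced.

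**2. Other standard methods at N=80.** The noncentral t version uses noncentrality √(N·r²/(1−r²)). The simulation applied the Pearson t-test to 400,000 bivariate normal samples.

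| Method | Two-sided | One-sided |
|---|---|---|
| Fisher z | 0.829 | 0.897 |
| Fisher z, bias-corrected | 0.833 | 0.900 |
| Simulation | 0.834 | 0.901 |
| Noncentral t (regression) | 0.847 | 0.911 |

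The most favourable case tried, one-sided noncentral t with r at 0.325 (the top of what rounds to 0.32), reaches 0.920.

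**3. N needed for 0.95 power.** N = ((z_α + z_β)/atanh(r))² + 3.
- Two-sided: (1.960 + 1.645)²/0.3316² + 3 = 121.2, so 122. Noncentral t gives 116.
- One-sided: (1.645 + 1.645)²/0.3316² + 3 = 101.4, so 102. Noncentral t gives 97.

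Against 80, the shortfall is 36–42 patients two-sided or 17–22 one-sided.

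**4. Could another input explain the line?**
- For 0.95 power at N=80 by Fisher z, r would have to be about 0.39 two-sided or 0.36 one-sided.
- Reading 0.32 as r² gives N of about 30–35. Reading it as a standardised mean difference gives about 106–127. Neither gives 80.
- At r=0.32, 0.90 power one-sided needs 81 by Fisher z or 77 by noncentral t. N=80 therefore fits a one-sided test at about 0.90.

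**5. Comparison with the preceding line.** The sampling-time correlation uses r²=0.10, so r is about 0.32, with 0.8 power one-tailed and N=56. One-sided noncentral t at r=0.32 returns 56. At that r, the same method needs 77 for 0.90 and 97 for 0.95. The neighbouring figure can be reproduced at almost the same effect size, which suggests an isolated slip.

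**6. What the 200 blood patients provide.** A loss of 20–25% leaves 200 × 0.80 = 160 to 200 × 0.75 = 150. If every retained patient had both NFL and WMHV, Fisher z power would be:
- N=150: 0.980 two-sided, 0.991 one-sided.
- N=160: 0.986 two-sided, 0.994 one-sided.

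To reach 0.95 by Fisher z, the share of retained patients who also need MRI is 122/160 = 76% to 122/150 = 81% two-sided, or 102/160 = 64% to 102/150 = 68% one-sided.

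**The case against.** The strongest reply accepts the arithmetic and disputes its importance. The working claim is that 80 is sufficient, and that survives: power is at least 0.83, above the 0.8 that the same section accepts for two other NFL calculations. Only the figure in brackets fails. This stands, and it makes the point a minor one.

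A reader might go further and infer that the study will stop at 80 NFL–WMHV pairs and so run a 10–17% risk of a false negative. The documents do not support that. Eighty is given as a sufficient number, not as a cap or stopping point. The planned numbers are 200 for blood and 300 invited to MRI.

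A reader might also infer that 200 blood patients are too few. That is not shown either. With full overlap the power for this effect exceeds 0.95. A shortfall is possible because patients are only invited to MRI and uptake is not stated, but nothing in the article demonstrates one.

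A third tempting step is to demand at least 122 paired patients, or to restate the power as 0.83 without qualification. Both presume a two-sided test. The line does not say so, the two calculations before it are one-tailed, and N=80 matches about 0.90 power one-sided. The article does not reveal whether the N, the power or an unstated input is the slip.

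Finally, being the primary imaging measure does not make WMHV the primary outcome of the study. The Outcome measures section gives that role, for cognition, to IC3 accuracy by domain at 1 year, which this error does not touch.

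**Conclusion.** The line is wrong as written on either sidedness. The stated power is too high by about 10–12 percentage points two-sided or 4–5 one-sided. Equivalently, the N falls short of what 0.95 power needs by 36–42 or 17–22 patients. This takes r=0.32 and alpha 0.05 as given and assumes a Pearson correlation under approximate bivariate normality.

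The consequence is limited. Power at 80 pairs remains above 0.80, and the conclusion about 200 blood patients is not shown to fail. For this effect at 0.95 power it is conditional on MRI overlap: about 116–122 (two-sided) or 97–102 (one-sided) of the 150–160 retained patients must have both measures. The article does not state that condition.

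**What to change.** State whether the NFL–WMHV test is one- or two-sided, then correct the line in one of two ways:
- keep N=80 and restate the power as about 0.83 (two-sided) or about 0.90 (one-sided); or
- keep 0.95 power and restate the N as 122 (two-sided) or 102 (one-sided) by Fisher z, counted as patients with both NFL and WMHV.

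The sponsor should choose according to the test intended. Next to the statement that 200 blood patients suffice, add that for this effect at 0.95 power it relies on that many of the 150–160 retained patients also having MRI.

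The cost is a change of wording, with one figure becoming less favourable. No extra enrolment and no change of analysis is needed.
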